### Secondary outcomes

#### Cognitive performance

Changes in cognition are assessed using a cognitive battery administered using the NeurOn online platform (https://neuropsychology.online). The following tests are included the following:

Reaction Time Test for motor function.Digit Span Test for executive function.Trail Making Test (Trails A and Trails B) for executive function.Sustained Attention to Response Test for executive function and attention.Word Encoding for episodic memory.Word Recognition for episodic memory.Go No-Go for executive function and impulse control.Fragmented Letters Test for visuospatial function.

Attention is an important secondary outcome as it was shown to improve in the short-term in our systematic review.^25^ Attention is measured by the Sustained Attention to Response Task (SART).^37^ In the SART test, participants have a visual presentation of 225 digits on a computer screen in a random order over a 4.3 min period (1150 ms between the onsets of digits) and are expected to respond with a key press except when they see the digit 3.^37 38^ It is a commonly used measure in research and is postulated to be sensitive to everyday attention tasks in traumatic brain injured patients as well as normal (control) individuals.^37 38^

#### Cerebral blood flow

CBF, also known as brain perfusion, can be affected by macronutrient composition^39 40^ and bioactives such as polyphenols,^41^ which are abundant in an MDP. Furthermore, reduced brain energy glucose metabolism and CBF is evident in major depressive disorders^42^ and cognitive decline,^43 44^ which is affected by food intake. An effect of intervention on CBF is proposed to partly underpin the effect of intervention on mood, anxiety and cognitive outcomes. We hypothesise a greater CBF after the MDP meal compared with the WD meal. MRI is considered the gold standard CBF measurement,^41^ with the following sequences used:

Time of flight angiography to determine the labelling plane to be used with pseudo-Continuous Arterial Spin Labelling (p-CASL).P-CASL which provides a means of quantifying regional CBF.^45^Magnetisation Prepared Rapid Gradient Echo (MPRAGE) for routine whole brain imaging using rapid acquisition.^46^Fluid-Attenuated Inversion Recovery (FLAIR) to visualise the white matter hyperintensities (WMH).^47^

MPRAGE and FLAIR sequences help to eliminate potential confounders influencing CBF in the present study such as atrophy and WMH.

Resting state functional MRI (rs-fMRI) is used to explore resting neural activity and connectivity between different brain regions including those that are concerned with self-referential processing and salience networks.^48^ During the scan, participants wear a pulse oximeter and respiratory belt to record the influence of cardiac and respiratory processes on measured signal. The scan parameters are taken from the UK-Biobank protocol,^49^ allowing a comparison to this large cohort. Analysis utilises physiological noise modelling, white matter/CSF signal regression and spatial independent components analysis to define resting state networks. Seed-based analysis utilises regions of interest (ROIs) for example, insular cortex, to determine whole brain connectivity. As part of a more extensive analysis, we will employ a Functional Connectivity Multivariate Pattern Analysis approach. This methodology allows us to rigorously test hypotheses across the entire functional connectome as it encompasses all voxel-to-voxel functional connections throughout the entire brain. This exploratory approach complements the seed-based method as it does not require a predetermined parcellation of the brain into ROIs.^50^

#### Blood pressure

Brachial BP is measured with the participant seated and following a 5 min rest period. Measurements are taken using an automatic BP monitor (Omron, 705IT) with an appropriately sized cuff. BP is measured three times and averaged in accordance with published guidelines.^51^

#### Biological samples

Blood, urine and faecal samples are collected at baseline (on day 1) and on completion of the 5 day intervention (on day 6 morning). Postprandial blood samples are collected after the day 1 test meal; 30 mL of blood is collected in three separate tubes (EDTA, Heparin, SST). Several blood biomarkers of mental and cognitive health as well as cardiometabolic health will be assessed including but not limited to plasma glucose, lipids, cortisol and select inflammatory markers and brain-derived neurotrophic factor. On arrival of the day 1 and day 6 mornings, the urine and faecal samples are frozen at −80°C for later analysis.

#### Gut microbial profile

The link between the gut microbiota and anxiety, depression,^52^ and cognition^53^ is evident through the gut–brain axis. Diet composition is an important modulator of microbiome composition and metabolism.^54^ The gut microbiome will be profiled using 16S rRNA Amplicon-based Metagenomic Sequencing of faecal samples.^55^

#### Metabolomics profile

Metabolomics are a tool for providing mechanistic insight into the response to dietary interventions.^56^ The influences of interventions on the metabolomics signature in serum and/or faecal samples will be explored using 1H-NMR-based untargeted metabolomics approach.^57^ Targeted metabolomics by Liquid Chromatography Tandem Mass Spectrometry will be used to measure both straight and branched short chain fatty acids, which are important mediators of gut–brain communication.^58^

#### Sleep timing, quality and quantity and circadian rest-activity rhythmicity

Due to the multidirectional relationship between sleep and circadian disturbances, anxiety and depression,^59^,^61^ cognition including alertness and attention^62^ and food intake,^63^ we will investigate the short-term effects of diet on sleep and circadian rhythmicity. By doing so, we also aim to eliminate the confounding effect of low sleep quality on mood and anxiety. The Pittsburgh Sleep Quality Index (PSQI) will be used to establish the initial sleep profile to detect sleep disturbances on day 0.^64^ Sleep quality is tracked during the two 5 day intervention periods using the Motion Watch 8, which is a wrist-worn actigraphy device. This will allow for the estimation of sleep timing, duration and quality as well as the amplitude and stability of circadian rest-activity rhythmicity known to be interlinked with mental well-being. The Karolinska Sleep Diary (KSD) is a subjective measure and used to estimate the duration, timing and quality of all sleep periods and will complement the actigraphy data to increase the accuracy of the objective sleep quality estimation.^65^ The Karolinska Sleepiness Scale (KSS) is administered every morning during the interventions alongside the KSD, to subjectively measure sleepiness. The KSS is a 9-point scale and asks the user to circle the number that represents the sleepiness level during the immediately preceding 5 min.^66^

#### Dietary behaviour

Participants will be sent the MEDAS questionnaire, 3 months after completing both arms to see if they have made any long-term change to their diets compared with the screening phase. They were also asked to rate how they found following the diets on a scale of 1–10.

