**Methods and analysis:**

Twenty-five UK adults (aged 18 or over) with mild to moderate anxiety and/or depression and low adherence to an MDP were recruited to a cross-over randomised controlled trial. Each participant undergoes a 5 day MDP and a 5 day WD in a randomised order with all meals provided. The co-primary outcomes are mood and anxiety, with secondary outcomes including cognitive function, brain perfusion (as assessed by MRI), sleep quality, blood pressure, plasma glucose, insulin, lipids, C-reactive protein, cortisol, brain-derived neurotrophic factor, gut microbiota speciation and microbial metabolites including short chain fatty acids. A linear mixed model and/or paired analysis will be used to compare the effects of treatments over time.

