### Eligibility criteria

Potential participants were recruited from the general population and from the University staff and students, using advertising posters/leaflets, internal emails and social media.

Twenty-five people aged 18 years or over were recruited. Participants were eligible if they met the following conditions:

Had mild to moderate level depression and/or anxiety, established using the Patient Health Questionnaire (PHQ-9) (score 5-14/27)^27^ and the Generalised Anxiety Disorder (GAD-7) (score 5-14/21).^28^ Both measures are commonly used in the NHS settings as preindicators of depression and anxiety.Were not already following an MDP, established using the Mediterranean Diet Adherence Screener (MEDAS) (score≤7/14) (online supplemental appendix 1).^29^Had been on the same dosage of their medication for at least 3 months and expected to keep a stable dosage for the next 3 months (for those who are on any antidepressant/antianxiety medication).Were eligible to undertake an MRI scan (eg, not having any possibility of pregnancy).Were not vegan or vegetarian.Did not have food allergies or intolerances to the food provided such as fish and nuts.

If participants reported antibiotics use in the last month, their participation was postponed until 1 month after treatment to allow the gut microbiota composition to return to its habitual status. Participants are requested to keep any probiotic supplement use and physical activity levels stable during their participation. For MRI safety, ‘any possibility of being pregnant’ or those with specific medical implants or devices (such as cardiac pacemakers or artificial limbs) were precluded from participating (online supplemental appendix 2, MRI Safety Screening Form). Participants were advised to discuss their participation with their general practitioners (GPs) and informed that the study researchers were going to inform their GPs about their participation (online supplemental appendix 3, Participant Information Sheet).

Table 1 lists the full inclusion and exclusion criteria.

**Table 1 T1:** The eligibility criteria

Inclusion criteria	Exclusion criteria
Males and females aged 18 or over	Vegan, vegetarian
Mild to moderate level anxiety and/or depression (PHQ-9 and/or GAD-7 scores of 5–14)	Allergic to any of the study components for example, nuts and fish

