Low MDP adherence (MEDAS score≤7/14)	On antianxiety and/or antidepressant medication which has changed in the last 3 months or likely to change in the next 3 months
Able to have an MRI scan	Unwilling or unable to make changes to their diet for 10 days (2×5 days period)
Computer literate with internet access	Unable to attend the intervention centre
Fluent in written and spoken English	MEDAS score>7
Gave consent for the study team to contact their GP	Not fluent in written and spoken English
Willing and able to comply with all study procedures including diet	MRI unsafety
	Not agreement for the study team to contact their GP
	Not prepared to make changes to diet for 10 days (2×5 days period)

GAD-7Generalised Anxiety Disorder (includes 7-item)GPgeneral practitionerMDPMediterranean-style dietary patternMEDASMediterranean Diet Adherence Screener tool (includes 14-items)PHQ-9Patient Health Questionnaire (includes 9-item)

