To capture their habitual dietary intake prior to the study, the participants are asked to complete the European Prospective Investigation into Cancer and Nutrition study Food Frequency Questionnaire (EPIC FFQ; https://www.epic-norfolk.org.uk/about-epic-norfolk/nutritional-methods/ffq/) before their baseline visit. To promote adherence, all study foods are delivered to participants’ homes using a supermarket delivery service, with extra food provided for the evening meals for one other person at home. Participants are provided with booklets (online supplemental appendix 6), with guidance as to how to store and prepare the meals and which additional foods and snacks can be consumed if hungry. The snacks are chosen to ensure they do not affect the MEDAS score of the study arm. To track dietary compliance, participants are asked to record all foods and beverages on the daily checklists in the booklets and provide notes and feedback. Participants are contacted daily to encourage dietary adherence.^31^

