### Outcomes

All outcome measures are summarised in table 4.

**Table 4 T4:** Summary of the outcome measures

	Measurement	Tool used	Time point	Time per measurement point	Location
Screening	Mood	PHQ-9	Prebaseline	9 min	Home
	Anxiety	GAD-7	Prebaseline	6 min	Home
	Initial dietary habits	MEDAS	Prebaseline	10 min	Home
During interventions	Initial dietary profile	EPIC FFQ	Baseline	30 min	Home
	Mood and anxiety	Bond-Lader VAS,POMS	Baseline, postprandial, 24 hours,day 6	30 min	Home (24 hours) and intervention centre (baseline, postprandial and day 6)
	Cognitive functions	NeurOn battery	Baseline, postprandial,day 6	30 min	Intervention centre
	CBF	MRI	Postprandial	30 min	UWWBIC
	Blood pressure		Baseline, postprandial,day 6	5 min	Intervention centre
	Blood samples		Baseline (≥10 hour fasting), postprandial,day 6 (≥10 hour fasting)	15 min	Intervention centre
	Urine and faecal samples		Baseline,day 6		Home collection kits are provided
	Weight and height	SECA scale	Baseline,day 6	5 min	Intervention centre
	Initial sleep profile	PSQI	Baseline	10 min	Intervention centre
	Sleep quality	ActigraphyKSDKSS	Over 5 days	Continuously (for actigraphy)5 min (for KSD and KSS)	Home
	Subjective dietary review score	Non-validated single question	Day 6		Intervention centre
Follow-up	Dietary behaviour	MEDAS	3 months	10 min	Home

CBFcerebral blood flowEPIC FFQEuropean Prospective Investigation into Cancer and Nutrition study Food Frequency QuestionnaireGAD-7Generalised Anxiety Disorder-7KSDKarolinska Sleep DiaryKSSKarolinska Sleepiness ScaleMEDASMediterranean Diet Adherence Screener tool (includes 14-item)PHQ-9Patient Health Questionaire-9POMSProfile of Mood StatesPSQIPittsburgh Sleep Quality IndexUWWBICUniversity of East Anglia Wellcome-Wolfson Brain Imaging CentreVASVisual Analogue Scale

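### The 3-month MEDAS change is measured from the same screening score that had to be 7 or below for entry, so regression to the mean biases it upward and may inflate, or be mistaken for, a lasting shift towards the Mediterranean diet

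*Protocol article*

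**What the plan says.** Under Eligibility criteria, the text requires that participants do not already follow a Mediterranean diet, "established using the Mediterranean Diet Adherence Screener (MEDAS) (score≤7/14"). Table 1 repeats this as an inclusion criterion, "Low MDP adherence (MEDAS score≤7/14"), and lists a score above 7 as an exclusion.

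Under Dietary behaviour, among the secondary outcomes: "Participants will be sent the MEDAS questionnaire, 3 months after completing both arms", with the stated purpose "to see if they have made any long-term change to their diets compared with the screening phase".

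Table 4 (Outcomes) lists the MEDAS at two points only: screening ("Initial dietary habits MEDAS Prebaseline 10 min Home") and the 3-month follow-up. The EPIC FFQ is completed before the baseline visit ("To capture their habitual dietary intake prior to the study"), but Table 4 does not list it at 3 months.

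The design gives no untreated comparison: "Each participant undergoes a 5 day MDP and a 5 day WD in a randomised order with all meals provided".

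**The concern.** One measurement does two jobs. It decides who enters, and it is then the reference value for change. A MEDAS score varies between occasions through reporting error and ordinary variation in diet. A ceiling at 7 admits people who scored below their usual level that day and turns away people who scored above it. Among those admitted, the screening mean is therefore too low as an estimate of their usual diet, and the next measurement is expected to be higher even if nobody changes.

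Two features could have removed this, and neither is present. A second MEDAS after selection but before the first diet would have given a reference free of most of the selection. A concurrent group without the intervention would have shown the same rise, which could then be subtracted. In this cross-over all participants have had both diets by the 3-month point, so the randomisation cannot help.

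At stake is the reading of this one follow-up outcome. The bias runs in the favourable direction, towards the Mediterranean diet.

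**Working it through.** **Plan's own figure.** The article states no effect size, SD, test or sample size for the 3-month MEDAS, so there is nothing to reproduce.

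**Inputs from the article.** Entry at MEDAS ≤7; reference is the screening score; 25 recruited with up to 20% dropout, so 25 × 0.80 = 20 completers. From arm 1 day 1 to the end of arm 2 is 28 + 5 = 33 days. The two scores are therefore more than four months apart, and perfect repeatability is not plausible.

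**Assumptions, not in the documents.** Pool of people screened: mean μ from 5 to 8, SD s = 2. Test-retest correlation ρ from 0.5 to 0.8. No true change in diet. Two-sided paired t-test at 0.05, so the nominal chance of a false rise is 2.5%.

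**Formulas.** With a bivariate normal model and the limit for whole-number scores at 7.5:
- c = (7.5 − μ)/s and λ = φ(c)/Φ(c)
- expected rise = (1 − ρ) · s · λ
- variance of the change = (1 − ρ)² · s² · (1 − cλ − λ²) + s² · (1 − ρ²)
- δ = rise × √20 / SD of change; chance of a false rise = P(noncentral t with 19 df and δ > 2.09)

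**One case in full (μ = 6, ρ = 0.7).** c = 0.75; λ = 0.3011/0.7734 = 0.389. Rise = 0.3 × 2 × 0.389 = 0.23. Variance = 0.09 × 4 × 0.556 + 4 × 0.51 = 2.24, SD 1.50. δ = 0.23 × 4.47/1.50 = 0.70, which gives a 10% chance of a falsely significant rise.

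**All cases (expected rise in points; chance of a false significant rise, n = 20).**

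| Pool mean | Share above 7 | ρ = 0.5 | ρ = 0.6 | ρ = 0.7 | ρ = 0.8 |
|---|---|---|---|---|---|
| 5 | 11% | 0.20; 7% | 0.16; 6% | 0.12; 5% | 0.08; 5% |
| 6 | 23% | 0.39; 14% | 0.31; 12% | 0.23; 10% | 0.16; 8% |
| 7 | 40% | 0.65; 32% | 0.52; 26% | 0.39; 20% | 0.26; 14% |
| 8 | 60% | 0.96; 61% | 0.77; 50% | 0.58; 39% | 0.39; 27% |

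**Check by simulation with whole-number scores.** The figures are slightly higher. The rise runs from 0.09 (mean 5, ρ = 0.8) to 1.00 (mean 8, ρ = 0.5). The chance of a false rise is 5–33% for means 5–7 and 29.8–64% for mean 8. The expected paired t exceeds 2.09 in only 2 of the 16 cases, both at mean 8: 2.43 at ρ = 0.5 and 2.14 at ρ = 0.6.

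**Sensitivity to the SD.** With SD 1.5–2.5, means 5–7 and ρ 0.5–0.85, the rise runs from 0.02 to 0.84 points and the chance of a false rise at n = 20 from about 3% to 34%.

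**The case against.** The best case for the plan has four parts.

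- **Size is unknown and may be trivial.** If few people screened score above 7, selection hardly bites: at mean 5 and SD 1.5 the rise is 0.02 to 0.08 points. The largest figures need a pool whose average lies above the cut-off, so that about 60% fail on MEDAS alone, and nothing in the article points to such a pool. This stands. Direction can be shown from the documents; size cannot.
- **The plan makes no strong claim.** It gives a purpose in one sentence. It sets no test or threshold and does not attribute any change to the Mediterranean diet. The outcome is absent from the Abstract's list of secondary outcomes and from the stated aim. Analysis detail may sit in a fuller document. This stands in part. The choice of reference is not left open, however: the article names the screening phase, and that choice causes the bias.
- **A repeat MEDAS would not rescue the outcome.** It would still be an uncontrolled before-after comparison of self-report in participants who know what they ate. That is correct. A repeat would remove most of the selection bias and nothing else.
- **The trial's main question is untouched.** That is also correct. Mood and anxiety are compared between diets within participants.

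A reader might go further and infer that regression to the mean on its own will look like a lasting dietary improvement, or that an ineffective intervention would be reported as one. The documents support neither. For pool means 5–7 a falsely significant rise is the less likely result in every case examined, and the article does not say what conclusion it would draw.

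**Conclusion.** The point holds as a minor one. The reference for the 3-month change is the selecting score, with no second pre-intervention MEDAS and no untreated group. The expected change with no true effect is therefore positive whenever the test-retest correlation is below 1. This can inflate a real shift or be mistaken for one.

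The size rests wholly on assumed inputs. Over pool means 5–8, SD 2 and correlations 0.5–0.8 it is about 0.1 to 1.0 points on a 14-point scale. The chance of a falsely significant rise with 20 completers is about 5–33% for means 5–7 and a little under 30% to 64% for mean 8, against 2.5%. The comparison with screening cannot by itself support a statement about long-term dietary change.

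**What to change.** Where it can still be collected, take one further MEDAS after enrolment and before arm 1 day 1, for example alongside the EPIC FFQ. Define the outcome as the 3-month score minus that value. The cost is one 10-minute online questionnaire per participant.

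The article gives data collection as June to December 2023 and the 25 participants as recruited, so this is probably no longer possible. In that case reword the Dietary behaviour paragraph to say that the comparison with screening is descriptive and uncontrolled, that it is subject to regression to the mean because of the ≤7 entry rule, and that no claim of long-term dietary change will rest on it. The cost is a sentence or two. Reporting the MEDAS distribution of everyone screened, including those excluded for scoring above 7, would let readers judge how large the artefact could be.

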### Statistical methods: data collection, management and analysis

#### Sample size calculation

The sample size calculation was based on data from a previous cross-over trial of the effect of MDP adherence in a young healthy adult group.^67^ Assuming an error rate of 0.05 and 90% power, we would require 15 and 20 participants to complete each arm for the primary outcome, which is the contentment, a mood domain from the Bond-Lader scale (9.6 unit expected difference, SD 10.3). To account for up to 20% dropout between random allocation to treatment sequence and study completion, we recruited 25 individuals.

#### Analysis

The main aim of the trial is to test if mood and anxiety can be improved over 5 days of intervention. The primary outcome analysis will use two-way repeated measures analysis with paired analysis taking mean change-scores.

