### Recruitment

Individuals who expressed an interest in the study were provided with the Participant Information Sheet and directed to the study website (https://app.mantal.co.uk/medimood), built on the Mantal platform, an online research management portal. First, participants were asked to provide consent (online supplemental appendix 4, Consent Form). Second, participants completed questionnaires to ascertain if they meet the study inclusion criteria detailed above. Those meeting the criteria were enrolled in the study and randomised to either an MDP or a WD for arm 1 of the study, by using random number generator in Microsoft Excel.

The study stages are displayed in figure 1.

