**Figure 2 F2:**
[figure not shown]
The protocol for the intervention centre visits. On the day 1 visit, participants undergo the full protocol. On day 6 visit, participants undergo the morning session only. CBF, cerebral blood flow; MDP, Mediterranean-style dietary pattern; WD, Western diet.

As menstruation-related hormonal fluctuations can cause disturbance in mood,^32^ neurocognitive functions^33^ and sleep,^34^ a wash-out period of 23-days was chosen to ensure female participants are on the same phase of their menstrual cycle on each intervention arm (ie, 28 days between arm 1 day 1 and arm 2 day 1).

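### The paired analysis of change-scores makes no period adjustment and no balancing of diet order is stated, so an arm 1 versus arm 2 shift in the change would bias or blur the diet contrast, depending on the realised split

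*Protocol article*

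**What the plan says.** The abstract (Methods and analysis) sets out the cross-over: "Each participant undergoes a 5 day MDP and a 5 day WD in a randomised order with all meals provided". The Recruitment section says the arm 1 diet was allocated "by using random number generator in Microsoft Excel" and mentions neither blocking nor fixed numbers per sequence.

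The Analysis section states: "The primary outcome analysis will use two-way repeated measures analysis", and continues "with paired analysis taking mean change-scores". The abstract words it differently: "A linear mixed model and/or paired analysis will be used to compare the effects of treatments over time". Neither place mentions period, sequence or order.

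The Interventions section justifies the gap between arms by menstrual phase: "a wash-out period of 23-days was chosen to ensure female participants are on the same phase of their menstrual cycle". In Table 4, mood and anxiety have their own baseline in each arm, whereas cerebral blood flow (CBF) is measured postprandially only.

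The sample size section gives the planning figures: "Assuming an error rate of 0.05 and 90% power", and for contentment "9.6 unit expected difference, SD 10.3".

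**The concern.** In a two-period cross-over, each person's MDP-minus-WD difference contains the diet effect plus or minus whatever separates arm 1 from arm 2. The sign depends on the order received. A plain paired test averages these differences over everyone. If one order is more common, part of the arm difference stays in the estimated diet effect. If the orders are equal in number, the arm difference cancels from the mean but still counts as scatter between people, so the test is conservative and the interval too wide.

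An arm difference in the change-score is plausible here, though its size is unknown:

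- **Mood and anxiety:** the arm 1 baseline is taken at the first clinic visit, after a blood draw. Apprehension could raise that baseline more than the arm 2 baseline and so alter the change.
- **Cognition (secondary):** the battery is taken three times per arm, and practice gains may be steeper in arm 1.
- **CBF (secondary):** with no baseline scan, a first-scan effect enters the contrast in full.

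The wash-out deals with cycle phase and gives time for carry-over to fade. It does nothing about a period shift.

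**Working it through.** **Inputs.** Difference 9.6, SD 10.3, error rate 0.05, power 90%, 15 and 20 completers, 20% dropout and 25 recruited all come from the sample size section. Assumptions: the test is two-sided, and 10.3 is the SD of within-person differences. The article gives no period shift, so a range of 2.5, 5 and 8 units is used.

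**Plan's own figure.** For a paired t-test with noncentrality (9.6/10.3)·√n, n = 14 gives 89.6% power and n = 15 gives 91.8%, so 15 is reproduced. The 20 cannot be checked, because only one effect and SD pair is given. Dropout: 20/(1 − 0.20) = 25.

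**Chance of imbalance, if allocation is simple.** With 25 people, 2·P(X ≤ 10) = 0.42 for 15:10 or worse. With 20 completers, 12:8 or worse has probability 0.50, 13:7 or worse 0.26, and 14:6 or worse 0.12. In relative terms 15:10 is the same imbalance as 12:8 (5/25 = 4/20 = 0.20); 14:6 is twice that (8/20 = 0.40).

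**Effect on the plain paired test.** Let d be the MDP change minus the WD change, τ the diet effect and π the arm 1 minus arm 2 shift in the change-score. Then E(d) = τ + π in order MDP–WD and τ − π in order WD–MDP.

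- Bias of the mean, given the split: π·(n1 − n2)/N. For 14:6 and π = 5 this is 5 × 8/20 = 2.0 units, or 2.0/9.6 = 21% of the planned effect.
- Expected sample variance of d: SD² + π²·[N/(N − 1)]·[1 − ((n1 − n2)/N)²]. For 10:10 and π = 5 this is 106.1 + 26.3 = 132.4, an SD of about 11.5 instead of 10.3.
- Type I error: the mean of d is normal with the bias above and variance SD²/N. Independently, the residual sum of squares over SD² is noncentral chi-squared with N − 1 degrees of freedom and noncentrality π²·N·[1 − ((n1 − n2)/N)²]/SD². The values below come from numerical integration; simulation agrees to within about 0.1 to 0.2 percentage points.

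| Split of 20 | Bias, shift 2.5 / 5 / 8 | Type I error, shift 2.5 / 5 / 8 |
|---|---|---|
| 10:10 | 0 / 0 / 0 | 4.4% / 3.0% / 1.4% |
| 12:8 | 0.5 / 1.0 / 1.6 | 4.9% / 4.5% / 3.7% |
| 14:6 | 1.0 / 2.0 / 3.2 | 6.3% / 9.5% / 13.8% |

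Averaged over all simple-randomisation splits, the bias is zero and the type I error is about 5% for each of these shifts.

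**Period-adjusted version.** Estimate: half the sum of the two sequence means of d. Standard error: (SD/2)·√(1/n1 + 1/n2), on N − 2 degrees of freedom. The shift π drops out, so there is no bias and the error is 5% at every split. Standard errors for 20 completers are 2.303 (10:10), 2.351 (12:8) and 2.513 (14:6), with power 97.6%, 97.1% and 95%. With 15 completers split 8:7, power is 91.4%.

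**The case against.** Four stronger readings are tempting, and the article does not support them.

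- **That the whole primary analysis omits period.** The article lists no model terms. Reading two-way as diet by time is natural from the abstract but is not stated, and a repeated-measures or mixed model specified elsewhere could include period. What stands is narrower: the paired comparison, which the abstract accepts as an alternative, has no adjustment as worded.
- **That any arm 1 versus arm 2 shift does harm.** The analysis uses change-scores, and mood and anxiety have a baseline in each arm, so a shift common to baseline and follow-up cancels. Drift after selection on raised PHQ-9 or GAD-7 scores starts at screening, and some of it precedes the arm 1 baseline. The day 1 MRI follows the postprandial mood testing, so the scan itself cannot affect those scores. CBF lacks this protection.
- **That the test is generally anti-conservative.** The bias is conditional on the split. Over repeated simple randomisation the plain paired test keeps its level, and at 12:8 its error is below 5%. The 42% chance of 15:10 or worse corresponds to that milder case; 14:6 or worse has a 12% chance.
- **That allocation was simple.** A spreadsheet generator can also produce a balanced list. The article neither states nor excludes this.

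It is also fair to say that the assumed shifts have no source in the article: 5 and 8 units are 52% and 83% of the planned effect. At 2.5 units the consequences are small. In a 10:10 split with a shift of 5, the unadjusted test still has about 96% power. None of this removes the case for adjustment. The trial has one realised split, and inference should hold given that split.

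**Conclusion.** The concern holds in a limited form. The paired change-score comparison leaves the diet contrast exposed to a period shift in the within-arm change (in the raw value for CBF), and nothing stated ensures equal orders. With 20 completers the harm runs from negligible (shift 2.5 at 12:8: bias 0.5, error 4.9%) to material (shift 5 or 8 at 14:6: bias 2.0 or 3.2, error 9.5% or 13.8%). Near-equal orders cause lost precision rather than bias. These figures rest on assumed shifts, on 10.3 being the SD of within-person differences, on a two-sided test and, for the probabilities, on simple allocation. The planned sample size is not in question. This is a correctable weakness that should be fixed, not a fatal flaw.

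**What to change.** State that period (arm 1 or arm 2) is a fixed effect in the mixed model. Where a paired analysis is used, replace the plain paired test with the average of the two sequence means of within-person differences, using the pooled within-sequence variance on N − 2 degrees of freedom. Apply this to the primary mood and anxiety contrasts and to the secondary diet contrasts, CBF in particular. State how the allocation list was generated, and report the numbers randomised and completed per sequence.

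The cost is one degree of freedom and no new data, so it can be done although data collection has ended; ideally it is recorded before the diet comparisons are examined. The 15, 20 and 25 need not change. If there is no shift, the loss at 20 completers is at most about 2.6 percentage points of power (97.7% to about 95%) at a 14:6 split, and close to nothing at 10:10.
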